## 6. STUDY SETTING

The study will be implemented in the real-world setting of Aboriginal primary health care services in South Australia. These services primarily provide primary health care to Aboriginal and Torres Strait Islander people. Each service is aware of the study.

## 7. STUDY POPULATION AND SETTING

### Training program:

The study population will be drawn from the services in Table 1 and includes:

- Aboriginal Health Workers and Practitioners
- Multidisciplinary health care providers

We will attempt to recruit a minimum of two participants from each site. There is no restriction on the maximum number of participants from each service.

### **Training program enablers and barriers interviews:**

A subsample of the training program participants. A purposeful sampling approach will be used to achieve a diversity in AHW/Ps and multi-disciplinary team members, working in urban, rural and remote services.

### **Service system assessment focus groups:**

Chronic disease team members in each service involved in the study. Focus groups with the chronic disease workforce in each participating health services will be conducted to assess the system characteristics for each service.

### **Medical record review:**

Participants will not be recruited; Medical records (existing data) of people with diabetes in each participating service who meet the inclusion criteria will be audited retrospectively.

## **8. ELIGIBILITY CRITERIA**

### **Inclusion criteria**

- 1. Training program:** Aboriginal Health Workers/Practitioners and multidisciplinary health care providers are eligible to participate in the study and must meet the following:

Aboriginal Health Worker/Practitioner:

- Completed or currently enrolled in Certificate III/IV in Indigenous Primary Health Care
- Employed by a participating South Australian Aboriginal primary health care service
- Provides diabetes care to Aboriginal clients.

Multidisciplinary health care provider who are:

- From a broad range of service providers, including enrolled and registered nurses, allied health professionals, medical doctors,
- Employed by or provides services in a participating South Australian Aboriginal primary health care service,
- Provides diabetes care to Aboriginal clients.

- 2. Interviews for enablers and barriers:** All participants in the training program are eligible to participate in an interview on the enablers and barriers to participation, effectiveness and sustainability of the training program.

- 3. Focus group for service systems assessment:** Chronic disease team of health services involved in the project.

- 4. Medical record review:** People with diabetes who have attended the participating health service and who fulfil the following criteria at the time of record review:

- Both male and female who are aged 18 years and over;
- identify as Aboriginal or Torres and Strait Islander people;
- have a confirmed diagnosis of T2DM and/or a HbA1c  $\geq 6.5$  mmol/L;

- have attended the health service at least twice in the preceding 12-month period;

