| Client level                                           | 
Eligibility criteria: People with diabetes who have attended the participating health service and who fulfil the following criteria at the time of record review meet the following criteria:
 
 
• Both males and females who aged 18 years and over;
 
• identify as Aboriginal or Torres and Strait Islander people;
 
• have a confirmed diagnosis of T2DM and/or a HbA1c <math>\geq 6.5</math> mmol/L;
 
• have attended the health service at least twice in the preceding 12-month period;
 
 
Those who meet the eligibility criteria become the study population in which the below variables are extracted.
 |
| Client ID                                              | Service unique record ID created and provided by the health service so that no identifying data is provided to the study team                                                                                                                                                                                                                                                                                                                                                                                                                                                                                                                                                                      |
| Month & Year of Birth                                  | To estimate age                                                                                                                                                                                                                                                                                                                                                                                                                                                                                                                                                                                                                                                                                    |

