| Pneumococcal vaccination up to date                                                                                                                                                                                                                                                                                                                                                                                                                                                                   | Vaccination status                                                                                                                    |
| Covid-19 vaccination                                                                                                                                                                                                                                                                                                                                                                                                                                                                                  | Vaccination status                                                                                                                    |
| Clinical measurements: 
 
– Cholesterol (mmol/L)
 
– LDL (mmol/L)
 
– HDL (mmol/L)
 
– Triglycerides (mmol/L)
 
– Creatinine (µmol/L)
 
– eGFR (ml/min/1.73m^2)
 
– uACR (mg/mmol)
 
– Random BGL (mmol/L)
- non-fasting, blood glucose test performed at the health service
 
– HbA1c (mmol/mol)
HbA1c (%)
 
– Systolic BPM (mm/Hg)
 
– Diastolic BPM (mm/Hg)
 
 | Identify proportion within recommended range                                                                                          |

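### The HbA1c entry threshold for the medical record review is given in mmol/L, a unit in which the protocol never extracts HbA1c, so the rule cannot be applied as written

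*Protocol*

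**What the plan says.** Protocol Section 8 (Inclusion criteria, item 4, Medical record review) limits the audit to adult Aboriginal or Torres Strait Islander people with diabetes who "have a confirmed diagnosis of T2DM and/or a HbA1c" of 6.5 mmol/L or more. They must also "have attended the health service at least twice in the preceding 12-month period". The client-level row of Section 10.d repeats the criterion with the same number and unit, and adds: "Those who meet the eligibility criteria become the study population in which the below variables are extracted".

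The clinical measurements row of Section 10.d lists HbA1c in two forms: "HbA1c (mmol/mol) HbA1c", the second entry being in %. In the same row mmol/L is used for cholesterol, LDL, HDL, triglycerides and random glucose ("Random BGL (mmol/L").

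Section 10.c (Medical record review) says that services use different patient management systems. Each extraction report will probably be written by the site's data manager or the software vendor. The file is de-identified before it reaches the study team.

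On timing, Section 8 applies the criteria to people "who fulfil the following criteria at the time of record review". Reviews are ideally at T1, T4 and T6 (months 6, 17 and 29), with the number negotiated per service. Section 11.a (Secondary Outcomes) plans counts, means and percentages, and differences between collection points.

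**The concern.** An entry criterion has to be turned into code, and this one cannot be. No HbA1c field exists in mmol/L, so whoever writes the extraction at a given service must guess. The number 6.5 could be set against the % field, the mmol/mol field or, by matching the unit, the random glucose field. These choices select different people. Because the extract arrives de-identified, a difference in coding between services would be hard to see centrally. The group that serves as denominator for quality of care and patient outcomes could then differ between services for reasons unrelated to care.

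A lesser question is whether the audited population stays the same from one review to the next. If it does not, a change in a mean or percentage can arise from a change in who is counted.

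**Working it through.** The Protocol states no sample size, power or alpha for the record review, so there is no such figure to reproduce. The check on the unit is a comparison of passages.

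**Unit**

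- Section 8, item 4: HbA1c at least 6.5 mmol/L.
- Section 10.d, client-level eligibility: HbA1c at least 6.5 mmol/L. The unit is the same in both places.
- Section 10.d, clinical measurements: HbA1c in mmol/mol and in %; mmol/L only for random glucose and lipids.

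The criterion's unit therefore matches neither HbA1c field. To show that the choice of field matters, assume the linear conversion mmol/mol = 10.93 × % − 23.5. This is not in the Protocol, and the mismatch does not depend on it.

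- 6.5 on the % scale: 10.93 × 6.5 − 23.5 = 71.045 − 23.5 = 47.5 mmol/mol.
- 6.5 on the mmol/mol scale: (6.5 + 23.5) / 10.93 = 30.0 / 10.93 = 2.7%.

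The same number on the two recorded scales marks very different levels. On mmol/mol, if recorded values run in the tens, nearly any recorded HbA1c would pass. Set against the glucose field, the rule would test a different analyte.

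**Who can be affected**

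The criterion is an and/or rule. A client with a confirmed type 2 diagnosis qualifies without an HbA1c value. The error can act only on clients without that diagnosis, and the Protocol does not give their share. It may not be nil, because Section 11.a plans to stratify patients by diabetes type.

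**Membership over time (caution only)**

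Inputs: randomisation at about month 6, after six months of the Peer Support Network (Section 10.b); reviews at months 6, 17 and 29; attendance look-back of 12 months.

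- T1: look-back from month −6 to 6; 0 of 12 months after randomisation.
- T4: look-back from month 5 to 17; 17 − 6 = 11 of 12 months after.
- T6: look-back from month 17 to 29; 12 of 12 months after.

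If eligibility is judged afresh each time, attendance at T4 and T6 rests almost wholly on visits made after randomisation. For illustration, let new entrants equal a fraction f of the continuing clients, with mean HbA1c lower by d points. The mean moves by f/(1+f) × d:

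- f = 0.05, d = 1.0: 0.05/1.05 × 1.0 = 0.048
- f = 0.10, d = 1.5: 0.10/1.10 × 1.5 = 0.136
- f = 0.20, d = 2.0: 0.20/1.20 × 2.0 = 0.333

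The values of f and d are assumed and have no source in the Protocol. The direction is assumed too: returning poor attenders could have higher HbA1c.

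**The case against.** The strongest reply on the unit is that this is a slip with little effect. The audit is limited to people with diabetes, a confirmed diagnosis is enough, both HbA1c fields are listed, and the study team will work with each site on the extraction. Much of this stands. A reader might infer that the cohort is mis-selected, but the documents show only that it could be, and only among clients without a confirmed type 2 diagnosis. What does not stand is that nothing needs doing. The listed criteria are the operational definition, the record review has no exclusion criteria, and different people are likely to code the rule at different sites.

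On changing membership, a reader might infer that redrawing the population after randomisation biases the comparison of Group A with Group B. The documents do not support that:

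- Redrawing is the natural reading of the eligibility text but is not stated. Table 3 describes retrospective extraction from January 2018, and a client ID is extracted.
- No scheduled review sets a trained group beside an untrained one. At T1 neither group has had the modules or onsite support; by T4 both have.
- Section 11.a states no between-group test for these outcomes.
- A diagnosis normally persists, so the rolling attendance rule, more than HbA1c, would drive turnover.

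Repeated cross-sections of current clients are also a recognised design for judging the care a service gives, and a closed cohort brings attrition. Section 14.c says client data will be collected and analysed in aggregate at service level, which sits uneasily with following individuals as the main analysis. The statistical analysis plan, not at hand, may settle the choice of design. These points reduce the membership issue to a caution.

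**Conclusion.** The unit error holds. Both statements of the criterion use a unit that fits neither extracted HbA1c field, so the rule cannot be applied as written. The consequence is a risk of inconsistent selection between services, confined to clients without a confirmed type 2 diagnosis. Its size cannot be calculated, because the Protocol does not give that group's share. The primary outcomes are measured on staff and are untouched.

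The membership point holds only as a caution. It rests on reading the criteria as applied afresh at each review. On that reading, the planned differences between time points may mix changed care with changed membership. The shift of 0.05 to 0.33 HbA1c points is illustrative, is not an estimate for this trial, and says nothing about a difference between the groups.

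**What to change.** The sponsor should reconcile the threshold and unit in Sections 8 and 10.d with the HbA1c fields in the extraction list, and state how the % and mmol/mol fields are each used, including when only one is filled. One coded rule should then go to every site and vendor. Which threshold and unit are intended is for the sponsor to confirm. The cost is a correction in two places and a short extraction specification.

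For the caution, report the number of new entrants at each review. Where the service-held client ID allows, add a sensitivity summary restricted to clients already eligible at T1. This needs a flag in the extract and a check that it fits the aggregate-analysis wording of the consent waiver in Section 14.c. The restricted summary will lose some clients to attrition, which is why it is proposed as a sensitivity summary and not as the main analysis.

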### **Exclusion criteria**

**Training program:** Limited or no access to stable Internet connection or computer hardware (laptop, desktop, tablet) can be provided by the health service.

**Interviews enablers and barriers:** No exclusion criteria

**Systems Assessments:** No exclusion criteria

**Medical record review:** No exclusion criteria

## **9. STUDY OUTCOMES**

### **a. Quantitative**

#### **i. Primary Outcome**

The primary outcomes of this study relate to diabetes management in a primary care setting that measure participant:

- **Knowledge** measured using the Simplified Diabetes Knowledge Scale – True/False Version [12]
- **Attitude** measured using the Diabetes Attitude Scale (DAS-3) [13].
- **Confidence** measured using the Diabetes Confidence Survey (DCS) [14].
- **Practice and skills** using case studies scenarios that were developed by the research team and the investigators specifically for the project and will be assessed as a composite outcome.
- **Skill** assessed using a case study for a diabetes foot check. This measure was adopted from the Foot Forward Project, which was developed by Twigg, Wischer, and Frank 2021 [15].

#### **ii. Secondary Outcome(s)**

The secondary outcomes of this study relate to patient care received and patient clinical outcomes:

- Peer Support Network satisfaction survey
- Interviews of enablers and barriers to participation
- Service systems assessment - Health Service Characteristics: System assessment through conducting focus groups with the chronic disease team staff to assess the system characteristics of each service using the Assessment of Chronic Care Scale (ACIC).
- Medical record review: Quality and Outcomes of diabetes care.

## **10. STUDY PROCEDURES**

### **a. Recruitment of participants**

**Training program:** All participants will be recruited prior to the commencement of the training program. Only staff employed in sites with a collaborative agreement signed by the service CEO (or delegate) will be approached.

Recruitment of training program participants will be by indirect approach. A manager of the primary health care service will identify eligible staff based on the eligibility criteria. Primary Health Care service CEO's or delegated clinic manager will send an email, drafted by the research team (Attachment 1) to potential participants who meet the inclusion criteria. The email will include an introduction to the training program, the information sheet and the consent form. Participants will be required to contact the research team to flag their interest in participating in the program. Contact details of the Study Manager are included on the information sheet and in the email.

In addition to individual discussions, the research team will offer to do a group onsite or zoom presentation about the project and what is required from participants. The site manager will invite participants to this and arrange a space for participants to join the zoom meeting or in person. At the group meeting participants will be invited to have an individual discussion about participating in the training program at another time. This will be arranged by a member of the research team and the potential participant. [name] the project lead will also be involved in the discussion. Potential participants will not be asked to consent to participate in the study at either of these discussions but given time to think about their participation.

**Interviews enablers and barriers:** All participants will be advised in the training program information sheet and participant consent form that they will be invited to participate in an interview about the barriers and enablers of the training program after they have completed the project. On completing the training program participants will be directly approached by email by a research team member up to three times over 3 weeks to be invited to participate in an interview (Attachment 2). We will seek to purposefully interview people across geographical locations and disciplines according to the sampling frame below. This will be dependent on participants, for example, there may not be nursing or allied health professionals across all geographical locations.

|                            | Metro | Rural | Remote |
|----------------------------|-------|-------|--------|
| Health Worker/Practitioner | 1     | 1     | 1      |
| Allied Health              | 1     | 1     | 1      |
| Nursing                    | 1     | 1     | 1      |

**System assessment:** The systems assessment is negotiated in the Collaborative Agreement with each service. If a service agrees to participate in the systems assessment, the CEO (or their nominee) will be provided by the Study Manager a draft email inviting diabetes/chronic disease team members to participate (Attachment 3). The participant information sheet will be attached. The CEO will arrange a time for the focus group inviting all of those they have identified as eligible. Only those interested in participating will turn up to hear about the study and the purpose of the systems assessment. Focus groups with the chronic disease workforce in each participating health services will be conducted to assess

the system characteristics for each service. There is no upper or lower limit to the number of staff who participate in the focus group; it depends on the staff willing to participate and who are available on the day.

**Medical record review:** Participants will not be recruited; existing data of people with diabetes in each participating service who meet the inclusion criteria will be audited retrospectively.

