## Sample

**Training program:** We will aim to recruit two participants per service. In discussions about the project with services, most services have more eligible staff. There must be at minimum one participant but is no upper limit to the number of participants from each service. The sample size will include an estimated uptake of (n=40) and accounted for drop-out rate of 50% of the AHW/P. Therefore, (n=20) participants would need to complete the training program.

**Interviews enablers and barriers:** We will aim to recruit between 3 and 15 participants of the training program given time and feasibility.

**Systems assessment:** The number of chronic disease staff who participate in the system assessment focus group will vary by service, depending on how large the team is and the number who consent to participate. There is no upper or lower limit to the number of staff who participate in the focus group; it depends on the staff willing to participate and who are available on the day.

**Medical record review:** Participants will not be recruited; Medical records (existing data) of people with diabetes in each participating service who meet the inclusion criteria will be audited retrospectively. The number of people with diabetes who receive care at each service enrolled in the study and meet the study inclusion criteria will vary. Prevalence of self-reported diabetes varies between 8 and 23% according to the 2018-19 ABS National Health Survey. It is therefore expected that between 8 and 23% of clients at each enrolled service will meet the eligibility criteria.

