### **Interviews enablers and barriers of participation, sustainability and effectiveness of the training program**

[name], an experienced qualitative researcher with a medical background, with support from a practicing Aboriginal Health Practitioner will conduct the interviews.

Interviews will be conducted face to face or by Zoom. If face to face, participants will be asked if they could arrange a space within their health service or if they would like the study team to arrange a space in public area such as a room in a local library or in another organisation. While all participants will be invited to participate in an interview, we will aim for a maximum of 15 participants given time and feasibility. If there is a choice (based on recruitment), we aim to have representation across geographic locations and service sizes and systems infrastructure, with a mix of AHW/Ps, Aboriginal nurses, and multidisciplinary staff. Participants will be asked permission for the interviews to be recorded. Interviews will be transcribed professionally, and participants will be invited to add or edit their transcript.

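### The interview approach is triggered by completing the training program, which conflicts with inviting all participants at T2/T4 and, read literally, leaves out those who stop early

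*Protocol*

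**What the plan says.** Protocol section 9 lists the interviews on enablers and barriers to participation as a secondary outcome. Table 3 extends their subject to sustainability and effectiveness.

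Section 10.a (*Recruitment of participants*) ties the approach to completion twice. Participants are told they will be "invited to participate in an interview about the barriers and enablers of the training program after they have completed the project", and then "On completing the training program participants will be directly approached by email by a research team member", with at most three attempts in three weeks. No other route to an interview is described there. The sampling frame in the same place crosses three disciplines with three locations, one person per cell.

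Other places set different rules:
- Section 10.c, interview procedures: "While all participants will be invited to participate in an interview", with a maximum of 15 interviewed.
- *Time period for recruitment*: four weeks for interview recruitment, which include the last two weeks of the program.
- *Data collection timepoints for secondary outcomes* and Table 3: interviews at T2 for Group A (8.5 months) and T4 for Group B (17 months).
- Section 8: "All participants in the training program are eligible to participate in an interview on the enablers and barriers to participation, effectiveness and sustainability", and "Interviews enablers and barriers: No exclusion criteria".

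The *Sample* section gives an uptake of 40, says it has "accounted for drop-out rate of 50% of the AHW/P", and concludes that 20 need to complete. It aims for 3 to 15 interviews.

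**The concern.** Someone who stops partway through the modules, or never attends Onsite Support, is well placed to say what the barriers to participation were. If staff follow the recruitment procedure as worded, that person never reaches the trigger. If they follow the interview procedures, the person is invited. Two teams working from the same protocol could therefore recruit different samples.

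At stake is whether the interviews can speak to barriers met by people who stopped, in a trial that expects substantial drop-out. A sample made up only of completers would report barriers that people overcame and could miss those that ended participation.

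**Working it through.** **1. The protocol's drop-out figure.** Inputs from *Sample*: completers needed 20, drop-out 50%. Required uptake = 20 / (1 − 0.5) = 40, which matches the stated 40. The inflation is done correctly.

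**2. The timing rules side by side.**

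| Place | Who is approached | When |
|---|---|---|
| 10.a Recruitment | those completing the program | on completion |
| 10.a Time period for recruitment | not restricted | 4 weeks, including the program's last 2 |
| 10.c Secondary-outcome timepoints, Table 3 | a cross-section by discipline (Table 3) | T2 (Group A), T4 (Group B) |
| 10.c Interview procedures | all participants invited | not stated |

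T2 and T4 are calendar points at the end of each group's training block. For Group A, 8.5 − 6 = 2.5 months after its start. For Group B, 17 − 14.5 = 2.5 months after its pre-training assessment. Both are close to the 10 weeks allotted. Taking the program here as that 10-week block, the recruitment window runs over weeks 9 to 12. An approach starting on completion at the end of week 10, with its three weeks used in full, would run to week 13, one week past the window.

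**3. Can the trigger be applied?** The protocol defines the training program as three components, one of them the Peer Support Network, which runs for months 1 to 17. A Group A AHW/P at T2 still has 17 − 8.5 = 8.5 months of the network ahead, so has not completed the program on that definition. Nor has the project ended, since follow-up runs to 29 months. Staff must choose a meaning for completion, and finishing the modules is a natural choice.

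**4. How many people are affected?** Let *m* of the 40 be AHW/Ps, and let *d* be the drop-out rate among multidisciplinary providers, which the protocol does not give. Expected non-completers = 0.5*m* + *d*(40 − *m*).
- *m* = 40: 20.
- *m* = 20 (assumed), *d* = 0: 10.
- *m* = 20 (assumed), *d* = 0.5: 10 + 10 = 20.

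The count depends on inputs that the document does not state.

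**5. Does the sampling frame protect against the gap?** The frame has 3 × 3 = 9 cells, none defined by completion. Section 10.c adds service size and systems infrastructure, again not completion. Even with everyone invited, a small sample may contain no non-completer. As an illustration, assume 20 of 40 are non-completers, acceptance is equal and interviewees are drawn at random. The chance of no non-completer among *k* interviewees is C(20,*k*)/C(40,*k*):
- *k* = 3: 1,140 / 9,880 = 0.115.
- *k* = 5: 15,504 / 658,008 = 0.024.

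Lower acceptance among non-completers would raise both. Under a strict completers-only approach the chance is 1.

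**The case against.** The strongest reply is that the disputed phrase only says when the email goes out. The same paragraph opens by saying that all participants will be advised of an interview invitation, section 10.c invites everyone, section 8 excludes no one, and the timepoints are calendar-based. On that reading people who stop early are invited with the rest. This is a fair reading, and the document does not rule it out. A reader might infer that those who drop out will definitely not be approached. That follows only from the strict reading of 10.a.

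Other stronger inferences also fail:
- *The trigger contradicts the eligibility rule.* Eligibility and time of approach are different rules. The direct conflict is with the invitation rule in 10.c and the calendar timing.
- *Twenty of 40 participants are shut out and every interviewee is a completer.* This needs the strict reading and also a 50% rate that covers everyone. The rate is attached to AHW/Ps, and multidisciplinary disciplines fill six of the nine frame cells. Drop-out is also undefined and may include formal withdrawals.
- *The secondary outcome is biased.* It is a purposive sample under inductive thematic analysis, with no estimate to bias.
- *The trial could not explain its own losses.* Facilitators' journals record barriers to uptake, network participation is logged, and AHW/Ps are surveyed after each session. These do not replace hearing from people who stopped, but they are information.

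The invitation email, information sheets and withdrawal form are attachments not shown, and may already be wider than the protocol text. What stands against the objection is that staff are given two rules, that completion is undefined, and that no sampling dimension secures non-completers. Nor is stopping the modules the same as withdrawing from the study, so many of these people could still be contacted.

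**Conclusion.** The point holds as an internal conflict with a practical consequence. The completion trigger in 10.a does not agree with the all-participants invitation in 10.c or with the T2/T4 and last-two-weeks timing. Read literally, it omits participants who stop early from an outcome about barriers to participation.

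The harm is selective coverage of 3 to 15 qualitative interviews. No numerical bias can be derived, because the document gives nothing on barriers by completion status. The number of people affected cannot be fixed either: 20 of 40 is right only if the AHW/P rate applies to all 40. The conclusion does not depend on that count. It rests on the wording of the four places compared and on drop-out being expected at all. The change is worth making, but the primary outcomes are untouched.

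**What to change.** - Reword the interview paragraph in 10.a. At the end of each group's 10-week training period (T2 for Group A, T4 for Group B), every enrolled participant is invited whatever their completion status, except those who have withdrawn and declined further contact. This keeps the timing already set elsewhere.
- Bring *Time period for recruitment* and the interview procedures in 10.c into line with that sentence, and check the invitation email and information sheets against it.
- Add completion status (completed; partial or stopped) to the purposive sampling frame, and hold some of the existing maximum of 15 places for non-completers. One person per frame cell uses 9 places, so up to 15 − 9 = 6 are not tied to a cell if the maximum is reached.

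The cost is wording in the protocol and any participant documents that repeat the trigger. The maximum number of interviews does not change. The downside is slightly fewer completer interviews and probably lower acceptance among non-completers, so some held places may go unfilled.
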